## 4. Interventions

As mentioned above, there will be three intervention arms: 1) a cognitively enriched walking program (Physical Activity (PA)+Cognitive Activity (CA)), 2) a walking program without cognitive enrichment (Physical Activity (PA) only) or 3) a passive control group (CG). The passive CG will receive no intervention program. Both the PA+CA and the PA program are group-based and will have a duration of six months (i.e. 24 weeks), with a frequency of two group sessions a week. All group sessions will last for approximately one hour and take place in groups of twelve or thirteen people supervised by a certified coach. Participants in both intervention groups (PA+CA and PA) will be encouraged to do one individual session every week, as well.

The PA+CA group will perform cognitive exercises while walking. One cognitively enriched walking session can be divided in three parts: (1) 5-10 minutes of brisk walking, (2) approximately 30-40 minutes of cognitive exercises while walking and (3) 5-10 minutes of cooling down (i.e. time for small talk or rest and relaxation). Cognitive exercises are exercises that are cognitively challenging and focus on multiple cognitive functions (i.e. attention, memory, executive functions, language, creative thinking) and can be performed while walking. Some examples are: planning a route, solving riddles, noticing, word fluency, bingo (i.e. noticing things along the walk),... These cognitive exercises have been developed in agreement with experts and the target population (Marent et al., 2021). Every cognitively enriched walking session, two to three cognitive exercises will be explained by the coach and performed by the participants. To this end, the coach receives a standardized manual with explanations of the different cognitive exercises. Furthermore, the coach will make sure that participants keep moving while performing the cognitive exercises. For the individual sessions, participants of the PA+CA group will receive practice cards with simplified instructions for all cognitive exercises that can be performed alone, with their partner, friends, or even grandchildren. Participants will be asked to register the number of individual cognitively enriched walks they perform in a personal log-book.

The PA group will walk for approximately the same amount of time and distance as the PA+CA group, but will not perform cognitive exercises. The coach will supervise and guide the group walk. These participants will also be asked to register the amount of individual walks they perform in a personal log-book.

The passive CG will not receive an intervention. Participants will be informed that they are assigned to the control group.

Participants will receive a letter at home with information about the intervention group they are allocated to (i.e. when will the sessions take place, where will they take place, contact information of the coach). Participants will be asked to be present for as many sessions as possible, but given the real-life context of this study, we will have the coaches track the attendance (in both the PA+CA and PA groups) so we can account for this in the analyses. The control group will receive information about why the use of a control group is important in intervention studies to keep them motivated to attend the following measurement sessions.

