## 2. Study design

To evaluate the effects of the cognitively enriched walking program on cognitive functioning (primary outcome), physical activity and psychosocial wellbeing (secondary outcomes), a randomized controlled trial (RCT) will be conducted. The intervention period will be 6 months, with measurements conducted at baseline, 3 months (mid-intervention), 6 months (post-intervention) and 12 months (follow-up). The interventions and measurements will take place at 2 university campuses in Belgium (Ghent and Leuven).

Participants will be allocated to one of the following intervention arms with a 1:1:1 allocation ratio: (1) cognitively enriched walking program, (2) walking program without enrichment, (3) passive control group. An investigator not involved in running the trial will generate the randomization sequence stratified by location (Ghent/Leuven) and availability (2 scheduling options for each location) using a statistical software program. Allocation will be disclosed to the researchers and participants only after completion of baseline measurements, ensuring double-blind data collection at baseline.

Furthermore, a process evaluation will be embedded in the RCT, using a mixed-methods design, and thus comprises questionnaires and focus group interviews. Questionnaires will be completed mid-intervention and post-intervention, focus groups will be conducted post-intervention.

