## 3. Participants

### 3.1. Recruitment

Participants for this study will be recruited by convenience and snowball sampling. Flyers with basic information on the study, the researcher's contact information (i.e. e-mail address and phone number), and name of the study's website will be distributed through different channels. Examples of these channels are local service centres, community health centres, stakeholders and organisations for older adults (e.g. OKRA, Vief, S-plus, Vlaamse Ouderenraad), social media and mail to people who previously showed interest in this program and provided their contact details (e.g. people that were not selected for participation in the pilot study but agreed to be kept informed about this study, people reached through an information day (Care4Brain) of the Leuven Brain Institute). On the website, we will share a brief summary of what is expected of study participants. Furthermore, our in- and exclusion criteria as well as our contact information will be listed on the website. It will also be stated that during an initial phone call, the in- and exclusion criteria will be discussed and that only with participants meeting these criteria, an appointment will be made for the baseline measurement. We will also try to specifically reach neighbourhoods of people with lower socioeconomic status, because these people are often less physically active. We will do this by distributing our flyers in community (health) centres in person, to have

a first personal contact with our potential participants. Furthermore, an advertisement will be placed in a local newspaper and/or on Facebook and we will organize live information sessions for all those interested. To ensure the handed information is understandable for everyone, we will use no specialist terms on our flyers or website.

We will also recruit coaches, who will supervise the sessions. These coaches will be hired, and thus paid, for their contribution to this project. To recruit them, will contact Wandelsport Vlaanderen saying that we are looking for certified walking coaches for this particular project, including a flyer that can be distributed. They will then contact the suited walking initiators and let us know who is interested in this project. By certified, we mean that the coaches have completed the training 'walking initiator' of Wandelsport Vlaanderen and Vlaamse Trainersschool.

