### Debriefing

All participants will be debriefed after the end of the study. This will be done by providing them with a report that will include information about the aim of this study and the different intervention conditions, the results of the study and their own performance during the study. It is practically and financially not feasible to organize the cognitively enriched walking intervention again for six months for the PA group and CG. Therefore, all participants will be given access to all intervention materials (e.g. the manual for the coaches) so they can try the cognitively enriched walking by themselves.

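### Nothing stops PA+CA participants sharing the practice cards with partners or friends in the other arms, so both PA+CA contrasts may be slightly diluted toward zero

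*Combined protocol and SAP*

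**What the plan says.** - **Recruitment (3.1).** "Participants for this study will be recruited by convenience and snowball sampling".
- **Allocation (2. Study design).** "Participants will be allocated to one of the following intervention arms with a 1:1:1 allocation ratio". The sequence is "stratified by location (Ghent/Leuven) and availability (2 scheduling options for each location"). Individual randomisation is implied rather than stated. No rule covers people who enrol together, and none of the ten exclusions in 3.2 concerns them.
- **Cards (4. Interventions).** PA+CA participants receive practice cards with simplified instructions for their individual sessions, for "all cognitive exercises that can be performed alone, with their partner, friends, or even grandchildren".
- **Place of the cards in the programme (4).** Both walking programmes run for 24 weeks "with a frequency of two group sessions a week". Participants in both "will be encouraged to do one individual session every week, as well". The cards therefore serve one of three weekly sessions.
- **Intended separation (4 and Debriefing).** The PA arm walks without the exercises and the control arm receives nothing. At debriefing, after the study, "all participants will be given access to all intervention materials". No sentence asks PA+CA participants to keep the cards from other trial participants before then.
- **Measurement (4, 5.2, 6.3).** The PA log-book counts individual walks. The process evaluation has no element for use of another arm's content, and its questionnaires and focus groups leave out the control arm. The per-protocol set keeps the control group without an exposure check.

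**The concern.** Three ordinary design choices combine badly. Snowballing works through social ties, so some participants will have a partner or friend in the trial. Allocation ignores those ties, so some pairs will have one member in PA+CA and the other in PA or control. The PA+CA member then takes home exercises that the protocol itself describes as suitable for doing with a partner or friend.

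If the exercises work and comparators use them, the intention-to-treat difference shrinks. The Introduction gives the aim as the added value of enrichment over walking. Only use in the PA arm affects that contrast; use in the control arm affects PA+CA versus control. A small or null difference would be harder to interpret, because no item in the plan records whether comparators used the exercises.

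**Working it through.** The plan gives no contamination figure, so there is none to reproduce. The size below is an illustration on stated assumptions.

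**Inputs from the documents**
- Recruited total of 149 (6.2). This is 124 × 1.2 = 148.8, rounded up.
- Four strata: two locations with two scheduling options each (2).
- Three arms, 1:1:1 (2).
- Effect size 0.30, taken from PA+CA versus control (6.2).
- One card-based session out of three a week (4).

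**Assumptions**
- Strata are of equal size.
- A fraction *c* of participants, 10% to 40%, has one partner or close friend in the same stratum.
- Every comparator whose tie is in PA+CA is exposed.
- Exposed comparators gain a share *s* of the effect, with *s* = 1/3 (one session of three) or *s* = 1 (upper limit).

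**Step 1. Stratum size.** 149/4 = 37.25 people, and 37.25/3 = 12.4 per arm. This agrees with the groups of twelve or thirteen in section 4.

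**Step 2. Chance that a comparator's tie is in PA+CA.** 12.4/36.25 = 0.342. For a tie in another stratum the chance is 1/3, so the same-stratum assumption matters little.

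**Step 3. Exposed share and dilution.** Exposed share = 0.342 × *c*. Diluted effect = 0.30 × (1 − 0.342 × *c* × *s*).

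| *c* | Comparators exposed | Shrinkage, *s* = 1/3 | 0.30 becomes | Shrinkage, *s* = 1 | 0.30 becomes |
|---|---|---|---|---|---|
| 10% | 3.4% | 1.1% | 0.297 | 3.4% | 0.29 |
| 20% | 6.8% | 2.3% | 0.293 | 6.8% | 0.28 |
| 40% | 13.7% | 4.6% | 0.286 | 13.7% | 0.26 |

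The percentage shrinkage applies to either contrast. The 0.30 column applies only to PA+CA versus control, because the documents give no effect size for PA+CA versus PA.

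**Step 4. How many pairs matter.** Two members of one stratum fall in different arms with probability 24.8/36.25 = 0.68. Pairs split between PA and control hold no cards. Pairs with exactly one PA+CA member make up 2 × 12.4 × 24.8/(37.25 × 36.25) = 0.46.

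**Step 5. Power, as an illustration only.** Section 6.2 does not state the effect-size metric, the test or the correlation, and 124 does not follow from the printed inputs alone. One set of assumptions does give 124, with power 0.803: a group-by-time interaction F test with f = 0.15 (0.30 halved), three groups, four times and correlation 0.2. If all effects are diluted equally, power at 124 is 0.79 for 1.7% dilution, 0.75 for 5% and 0.70 for 10%.

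**The case against.** The strongest reply is that the arms are well separated where it counts. Section 5.2 gives each walking arm its own groups and coaches. The coached sessions, which carry two thirds of the weekly programme, cannot leak through a card. The cards hold simplified instructions for one encouraged session a week, and section 4 speaks of partners and friends in general, not of co-enrolled participants. Any bias is toward zero, so it cannot create a false benefit, and the trial is meant to reflect real life. All of this stands. It limits the size of the problem but leaves the home route open.

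A reader might infer more than the documents support:
- **That comparators receive the enriched programme, or that bias is certain.** The text shows an open route to part of the content. It does not show that anyone uses it.
- **That control-arm use weakens the added-value contrast.** It does not enter PA+CA versus PA.
- **That most couples are contaminated because most are split.** About 68% are split, but only about 46% have exactly one PA+CA member.
- **That people from the pilot arrive with the programme already behind them.** Section 3.1 mentions "people that were not selected for participation in the pilot study but agreed to be kept informed about this study", which is the opposite group. The pilot's content is not described, and any former pilot participants would be randomised across all three arms.
- **That no relevant data exist.** Section 5.3 repeats the cognitive-function questionnaires at each visit, and these appear to include the cognitive activity scale (CLAS). PA participants also complete process questionnaires. Neither asks specifically about the exercises, and the primary-outcome model in 6.4 uses only baseline cognitive activity, as a covariate.

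**Conclusion.** The concern holds as a possible, probably small, dilution toward zero that the plan neither prevents nor records. On the stated assumptions, 3% to 14% of comparators could be exposed. The contrasts would shrink by about 1% to 5% if the cards carry one third of the effect, and by at most 14% if they carry all of it. Under the illustrative reconstruction of 124, a 5% dilution costs about 5 percentage points of power. The direction depends on comparators using the exercises and on the exercises working. The size depends on *c* and *s*, for which the documents give no value. This does not threaten the trial's validity. It is worth acting on because prevention is nearly free and unrecorded exposure cannot be quantified afterwards.

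**What to change.** 1. In section 4, on the cards and in the PA+CA allocation letter, tell PA+CA participants not to do the exercises with, or pass the cards to, anyone else enrolled in the trial until the 12-month visits are complete. Use with people outside the trial can stay as described.
2. At the baseline visit, before allocation is disclosed, record whether a partner, household member or friend is also enrolled.
3. At 3, 6 and 12 months, ask PA and control participants in neutral wording whether they used the exercises.
4. In 6.4, pre-specify a report of these answers by arm and a sensitivity analysis. Restricting to participants with no enrolled tie at baseline keeps the randomised comparison. Dropping comparators by reported use does not, because use arises after randomisation.

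The cost is one sentence, a few short questions and one extra analysis.

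Allocating households together is not recommended. It would create clusters that the participant-level random intercepts in 6.4 and the sample size in 6.2 do not handle, and it would leave out friends.

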## 1. Introduction

Dementia currently affects more than 47 million people worldwide, its prevalence is forecasted to triple by 2050, and it has been reported to be one of the most costly disorders in Belgium.

There is good scientific evidence that the cognitive impairments associated with the development of dementia can be lessened or even reversed thanks to the plasticity of the brain (rewiring). Recent research has shown that physical activity combined with performing cognitively challenging tasks is a very potent way to induce this rewiring of the brain, which can enable people to improve their cognitive functions. Yet, so far, these studies are mainly limited to controlled laboratory conditions. Our team developed a real-life cognitively enriched walking program, with input from experts and end-users.

In this study, we will examine the added value of enriching physical activity (walking) with cognitive exercises in improving cognition of older adults by conducting a six-month community-based randomized controlled trial. We will also examine the longer term effectiveness in a follow-up measurement visit six months after the program. We will focus on the following outcomes: cognitive functioning (i.e., objective, subjective and cognitive activity), psychosocial wellbeing (i.e., loneliness, social support, depressive symptomatology, positive wellbeing and expectations regarding aging), physical activity (i.e. both objective and subjective) and general health.

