### General health

- *The Patient-Reported Outcomes Measurement Information System (PROMIS) eight-item short form for General Health (Pellicciari et al., 2021)*: this is a self-report measure for global self-rated health with acceptable psychometric properties. This questionnaire provides us with a total score as well as distinct scores for mental and physical health.
- *The Patient-Reported Outcomes Measurement Information System (PROMIS) four-item short form for Sleep Disturbances (Buysse et al., 2010; Terwee et al., 2014)*: this self-report measure with good psychometric properties assesses quality of sleep and prevalence of sleep difficulties.

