### Baseline visit

First, the informed consent will be signed. At this moment, participants can also ask questions at the researcher if they have any after reading the information letter. During the baseline visit, the MoCA and BDI-II will be administered as a secondary screening for possible cognitive difficulties and depressive symptomatology, respectively. As mentioned above, participants excluded from the study at this stage will be informed about the deviant score by the either the PhD student or the postdoctoral researcher. Furthermore, the person will receive a letter that they can bring at their next appointment with their general practitioner. The letter will (1) contain the description of the test and the score obtained and an explanation that there are multiple possible reasons for such a score, and that only one of them is (mild) cognitive impairment or depressive symptomatology and (2)

indicate that, in case the general practitioner thinks this is necessary, an appointment can be made with a memory clinic or psychologist.

Included participants will be asked to provide sociodemographic information (i.e. age, gender, length, weight, nationality, country of origin, educational level, marital status, longest held profession, and income) during this baseline visit. Furthermore, participants will be asked if there is any relevant medical information the coaches need to know to ensure safety of the waling sessions (i.e., so the coach can anticipate any possibly dangerous situations).

Participants will also be asked to complete the questionnaires regarding cognitive function, psychosocial wellbeing, physical activity and general health described above (see *outcomes*). Objective cognitive and physical activity will be measured at baseline as well by administering the CANTAB and wearing an accelerometer for seven consecutive days (day + night), respectively. Participants will be asked to return the accelerometer by delivering it to the office of one of the researchers or by returning it by post (pre-paid by the research team).

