### **Follow up visit**

Six months after the intervention end, so twelve months after the intervention start, there will be one last follow-up visit. The procedure is again the same as that of the second and third visit, except that participants will not have to complete a process evaluation questionnaire. Again, we will ask participants to return the accelerometers by delivering it to the office of one of the researchers or by returning it by post (pre-paid by the research team).

[figure not shown]

Figure 1. Procedure

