### 6.3. Populations for analyses

The data set will be analysed according to the ‘intention to treat’ (taking into account everyone who was assigned to an intervention arm) and ‘per protocol’ (taking into account only those who received  $\geq 75\%$  of the intervention, and the control group) principle.

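### No systematic recording of falls or injuries is described in any arm, so the trial cannot report harms of enriched walking against plain walking or control

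*Combined protocol and SAP*

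**What the plan says.** **Session records.** Section 4 gives each walking arm a log-book. For the enriched arm (PA+CA), "Participants will be asked to register the number of individual cognitively enriched walks they perform in a personal log-book". For plain walking (PA), "These participants will also be asked to register the amount of individual walks they perform in a personal log-book". For group sessions, "we will have the coaches track the attendance (in both the PA+CA and PA groups) so we can account for this in the analyses". Nothing equivalent exists for the control group, which has no sessions.

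**Outcomes.** The Introduction opens its list with "We will focus on the following outcomes: cognitive functioning" and continues with psychosocial wellbeing, physical activity and general health. Section 5.1 measures general health with PROMIS: "this is a self-report measure for global self-rated health with acceptable psychometric properties".

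**Visits.** Section 5.3 specifies questionnaires, CANTAB and accelerometer at every visit. For the 12-month visit it says "The procedure is again the same as that of the second and third visit", apart from the process questionnaire.

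**Safety.** The one safety step described is at the baseline visit, where relevant medical information is collected "so the coach can anticipate any possibly dangerous situations".

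**Analysis.** Section 6.3 sets an intention-to-treat population and a per-protocol population, the latter "taking into account only those who received" at least 75% of the intervention, plus the control group. Section 6 has no harm hypothesis, safety population or harm table.

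**The concern.** The two walking arms are matched on approximate walking time and distance, so the contrast between them isolates the cognitive task. In the enriched arm, people aged 65 or over do that task for some 30 to 40 minutes of each group walk while the coach keeps them on the move, and they are encouraged to add a weekly individual session. After the trial, every participant receives the intervention materials to use on their own (Section 4, Debriefing). A reader weighing a cognitive gain would want to know whether it came with more falls or injuries.

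The plan as written cannot answer that, either against plain walking or against control. It also leaves the per-protocol result harder to read. A walker who stops after an injury and one who loses interest leave that set in the same way, with no reason planned to be recorded. Events not asked about during the trial cannot be recovered reliably afterwards.

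**Working it through.** The plan states no figure on this point, so there is none to reproduce. The check has three parts.

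**1. Every place where an event could be recorded**

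| Record | Arms | What it holds |
|---|---|---|
| Attendance list (Section 4; Table 1) | PA+CA, PA | Presence at group sessions |
| Log-book (Section 4) | PA+CA, PA | Number of individual walks |
| Process questionnaires, 3 and 6 months for participants (5.2) | PA+CA, PA, coaches | Fidelity, dose, acceptability, context; some open questions |
| Focus groups, after the intervention (5.2) | PA+CA, PA, coaches | Qualitative themes |
| PROMIS general health (5.1) | All | Self-rated score |
| Accelerometer diary (5.1) | All | Times and reasons for non-wear in a seven-day window |
| Visit procedures (5.3) | All | No question on falls or injuries |

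The records that cover all three arms are not event records. Those that could carry an incident exclude the control group and yield no count.

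**2. Exposure without a described event record**

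Inputs: 24 weeks, two group sessions and one encouraged individual session a week, groups of 12 or 13 (Section 4); four groups per walking arm (Section 5.2, Focus groups).

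- Per walker: 24 × 2 = 48 group and up to 24 × 1 = 24 individual sessions, 72 in all.
- People per walking arm: 4 × 12 = 48 to 4 × 13 = 52. This agrees with 149 / 3 ≈ 50 from Section 6.2.
- Group person-sessions per arm: 48 × 48 = 2,304 to 52 × 48 = 2,496.
- Individual person-sessions per arm, at most: 48 × 24 = 1,152 to 52 × 24 = 1,248.
- Both walking arms: 2 × (2,304 + 1,152) = 6,912 to 2 × (2,496 + 1,248) = 7,488.

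For the per-protocol rule, assume that 75% refers to the group sessions (Section 6.3 does not say). The threshold is then 0.75 × 48 = 36. Missing 13 sessions, or 13 / 2 = 6.5 weeks, removes a walker.

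**3. What uniform recording would deliver**

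Take n = 49 per arm. The documents give no fall proportions, so 10%, 20% and 30% are assumptions.

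- Zero events in an arm, one-sided 95% upper limit: 1 − 0.05^(1/n) = 5.9% for n = 49. With 124 / 3 ≈ 41 per arm it is 7.0%.
- 95% half-width for PA+CA minus PA with equal proportions p: 1.96 × √(2p(1 − p)/n). This gives 11.9, 15.8 and 18.1 percentage points for p = 10%, 20% and 30%.
- Power of a two-sided 5% test of two proportions: 28% for 10% against 20%, 58% for 20% against 40%, and 86% for 30% against 60%.

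**The case against.** **Unseen material.** The coach questionnaires and interview guides are additional files that were not available, the list of questionnaire topics is open-ended, and Table 1 names a registration form whose content is not described. Incident reporting may exist there. This stands, and it limits the claim to what the documents describe. It does not restore a comparison with control, because these tools belong to the walking arms and coaches.

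**Incidents could surface.** A reader might infer that a hazard in one of the eight walking groups could reach the researchers through no planned record. The documents do not support that. Questionnaires include open questions and environmental context, coaches identify their group by city and days, and a focus group is planned for each walking group and for each set of coaches. Much of this comes after the intervention, and none of it is a count.

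**Scope.** The stated aim is improvement in cognition. Harm is not an objective that the plan sets and then fails to meet. The baseline question about medical information is a precaution, not a statement that the sessions are dangerous. Both points stand; this is a gap, not a contradiction.

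**Ascertainment.** A reader might infer that informal reports would bias the comparison of enriched with plain walking. Those arms share the same structure of coaches, attendance lists, log-books and questionnaires. Unequal ascertainment is a problem only for comparisons with control.

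**Per-protocol loss.** The intention-to-treat analysis keeps walkers who stop after an injury. That is correct, but the reason for stopping stays unknown in either analysis.

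**Number of falls missed.** It is tempting to put a figure on this. The documents give no fall rate, and a rate for all falls over 12 months would say little about falls during sessions, so no such figure is offered.

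**Conclusion.** The concern holds in this form: the documents describe no systematic recording of falls or injuries in any arm, and no record of why a walker drops below the per-protocol threshold. Followed as written, the plan yields no harms comparison for either contrast. The exposure concerned is at most 6,912 to 7,488 planned person-sessions. The individual third of that (24 / 72) is an upper bound, because those sessions are only encouraged.

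The conclusion rests on the available text and could soften if the unseen files contain an incident record for the walking arms. It does not touch the validity of the cognitive comparison. Nor would recording make this a powered safety study; at about 50 per arm only large excesses could be shown. The change is still worth making, because it is cheap and the information is otherwise lost.

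**What to change.** 1. At the existing 3-, 6- and 12-month visits, ask all three arms the same short question: falls, and injuries needing medical care, since the last visit, and whether each happened in a group session, in an individual session or elsewhere.
2. Add two columns to the attendance list (event in session; reason for absence or stopping) and one to the log-book (event in session). Coaches pass in-session injuries to the research team.
3. Add to Section 6.4 a descriptive table of counts with confidence intervals by randomised arm, with the number answering at each visit. Use the visit question for between-arm comparison, because it is asked identically in every arm.
4. List the reasons for falling below 75% beside the per-protocol result.

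The cost is a few minutes at three visits, three form columns and one table. No extra visit, assessor or procedure is needed. The downside is imprecision, which the report should state.
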